### Blinding

Data managers (including the telephone interviewer during the follow-up period) and statisticians will be blinded to participant group assignment. Therapists, data managers, and statisticians will not be allowed to communicate with others about the participants’ allocation.

### Participants

#### Study population

Patients with ischemic stroke who present with constipation will be recruited from the acupuncture and moxibustion departments of the Beijing Hospital of Traditional Chinese Medicine Affiliated to Capital Medical University in Beijing, China.

#### Sample size

Since there are no previous three-armed randomized controlled trials that investigate this topic, the present study will provide effect size data for sample size calculations of subsequent large-scale randomized controlled trials. For practical reasons, a sample size of 40 per group and a total number of 120 participants will be recruited during the entire study according to outpatient and inpatient censuses of the hospital.

#### Recruitment and baseline assessment

Researchers will recruit participants from outpatient clinics and inpatient wards of the acupuncture and moxibustion departments. Recruitment posters will be posted in the hospital. The posters will contain a brief, Institutional Review Board-approved introduction to the study, the participants, the interventions, and contact information for the researchers. The recruitment information will also be uploaded to the hospital website (http://www.bjzhongyi.com).

Consent will be obtained by one of the investigators, with a witness present. Following written informed consent, eligible patients will be asked to complete a general information form including name, gender, age, medical history, etc. and complete a 1-week defecation diary as the baseline assessment. A neurologist will determine the Glasgow Coma Scale score and the National Institute of Health Stroke Scale score for each participant and these scores will be used to decide whether to include the patient in the study according to the inclusion and exclusion criteria. Personal information about potential and enrolled participants will be collected and maintained confidentially.

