#### Inclusion criteria

Inclusion criteria are a diagnosis of ischemic stroke according to the diagnostic criteria specified by the World Health Organization [23], constipation symptoms according to the Rome IV Functional Constipation Criteria [24], 2 weeks to 6 months after stroke onset, aged between 30 and 75 years old, Glasgow Coma Scale score ≥ 7 and National Institute of Health Stroke Scale ≤ 21, no previous medical history of constipation before stroke onset and symptoms of constipation present for at least 2 consecutive weeks after stroke, no use of gastrointestinal drugs 1 week before randomization (except for emergency drugs), no acupuncture treatment for constipation in the previous 2 weeks, and signed informed consent form.

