### Outcome measures

#### Primary outcome measure

The primary outcome measure will be the change in the weekly mean number of CSBMs over the 4 weeks of the intervention and the 4 weeks of the follow-up. A CSBM is defined as a SBM unrelated to the administration of laxatives or finger manipulation, accompanied by a self-reported feeling of complete evacuation. Bowel movements achieved with the help of glycerin, enemas, or finger manipulation are not considered spontaneous. If bowel movements occur within 24 h after the intake of laxatives, they will not be considered spontaneous. However, if bowel movements occur more than 24 h after administration of laxatives, they will be considered spontaneous. The total number of CSBMs during the treatment period and follow-up period will be averaged to obtain mean weekly CSBMs.

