#### Secondary outcome measures

The change in the number of mean SBMs that are unrelated to the administration of laxatives or finger manipulation, with or without a self-reported feeling of complete evacuation. This measure will be calculated in the same way as the CSBMs.The change in mean stool consistency score, as per the Bristol Stool Scale (Table 1). The score will be recorded according to the stool type (e.g. type 1 = 1 point, type 2 = 2 points, etc.) to obtain mean stool consistency scores. The Bristol Stool Scale is a widely used form authored by Dr. K Heaton, reader in medicine, University of Bristol. It can be downloaded from the website https://www.bladderandbowel.org/bowel/bowel-resources/bristol-stool-form-scale/ representations of the different types of stool will be included in the patients’ diaries and serve as visual comparators. A patient will record the type of stool in their diary according to the picture.The change in mean straining scores during defecation. The severity of straining will be graded using a 5-point ordinal scale: 0 = absent, 1 = mild, 2 = moderate, 3 = severe, and 4 = very severe.The change in weekly frequency of laxative use. This includes the total number of times that laxatives are used during the 4-week treatment period and the 4-week follow-up period. Instances of laxative use will be summed and divided by 4 to obtain the weekly frequency during the two periods.

**Table 1 Tab1:** Bristol Stool Scale

Type	Description
1	Separate hard lumps, like nuts (hard to pass)
2	Sausage-shaped, but lumpy
3	Like a sausage but with cracks on its surface
4	Like a sausage or snake, smooth and soft
5	Soft blobs with clear-cut edges (passed easily)
6	Fluffy pieces with ragged edges, a mushy stool
7	Watery, no solid pieces; entirely liquid

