### Statistical analysis

The analysis of the primary outcome will be based on both a full analysis (intention-to-treat analysis) and per-protocol sets (per-protocol analysis). The analyses of secondary outcomes will be based on the per-protocol sets. The full analysis set refer to the participants who are randomized and receive at least one treatment session. Any missing data will be replaced by the last measured value. The per-protocol sets will be defined as the participants who receive all treatment sessions and completed the study according to the protocol.

The statistical analysis will be performed by a statistician who is blinded to participant group allocation and will not be involved in other aspects of the study. The SPSS statistical package (version 18.0, International Business Machines Corporation, China) will be used to analyze the data. All data will be kept in duplicate by specific researchers. The results of the quantitative data analyses will be presented as means ± standard deviation. The Kolmogorov–Smirnov test will be applied as the normality test for quantitative variables. The Wilcoxon test or analysis of variance (ANOVA) will be used to compare the difference between groups according to the results of the Kolmogorov–Smirnov test. The results for categorical data will be compared with the chi-squared test and presented as a percentage. The statistical significance level will be set at 0.05 (two-sided) with a 95% confidence interval.

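### The change scores for stool consistency and straining are undefined for a participant who passes no stool in the 1-week baseline diary, and the carry-forward rule cannot supply the missing baseline

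*Protocol article*

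**What the plan says.** All references are to the protocol article.

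- **Baseline window.** Under Recruitment and baseline assessment, patients who have consented are to "complete a 1-week defecation diary as the baseline assessment". Under Randomization and allocation concealment, the envelope is opened only after the baseline measurements.
- **The two outcomes.** Secondary outcome measures lists "The change in mean stool consistency score, as per the Bristol Stool Scale" and "The change in mean straining scores during defecation". For consistency, "The score will be recorded according to the stool type". Straining is graded "0 = absent, 1 = mild, 2 = moderate, 3 = severe, and 4 = very severe".
- **Missing data.** The only rule, under Statistical analysis, is "Any missing data will be replaced by the last measured value". Secondary outcomes are analysed in the per-protocol set, whose definition does not mention having a baseline score.
- **Laxatives around baseline.** Inclusion criteria require "no use of gastrointestinal drugs 1 week before randomization (except for emergency drugs"), so emergency drugs are possible in the week before randomization. The Intervention section permits emergency laxatives after 4 or more days without a spontaneous movement.
- **Which stools count.** For the spontaneous counts, "Bowel movements achieved with the help of glycerin, enemas, or finger manipulation are not considered spontaneous". No such restriction, and no explicit inclusion, is written for the consistency or straining scores.

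**The concern.** A count has a natural zero, so a week without a stool is a valid observation for complete spontaneous movements, spontaneous movements and laxative use. A Bristol or straining mean has no such zero. With no stool there is nothing to score, and the straining grade of 0 describes a stool passed without straining, not the absence of a stool.

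The trial enrols constipated patients, takes baseline from a single 7-day diary, and does not require a bowel movement in that week. An empty week is therefore foreseeable. When it happens, the outcome definition, the baseline window and the missing-data rule together yield no value.

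What is at stake is who contributes to these two outcomes. An empty week is more likely in a more severely constipated participant, so any analysis limited to computable changes describes a milder group than the one randomized. This matters somewhat more in a pilot whose stated purpose, in the Discussion, is to inform later sample sizes through effect sizes, variability and data completeness.

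**Working it through.** **1. The plan's own figure.** The article gives 40 per group and 120 in total, set for practical reasons: 3 × 40 = 120, which agrees. It states no effect size, SD, power or baseline stool rate, so there is no power calculation to reproduce.

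**2. Following the rules as written.** Change = period mean score − baseline mean score. With no stool in the baseline week, the baseline mean is a sum over no stools divided by zero. Carry-forward needs an earlier measurement, and none exists before baseline. The change is undefined, however complete the later diary is.

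**3. How often the week could be empty.** The weekly mean m is an assumption. With no emergency laxative, the probability of no stool in 7 days is exp(−m) under a Poisson model. Under a negative binomial with k = 2, which allows patients to differ in their rates, it is (2/(2 + m))².

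| Assumed m per week | Poisson | of 40 | of 120 | Negative binomial, k = 2 | of 120 |
|---|---|---|---|---|---|
| 1 | exp(−1) = 36.8% | 14.7 | 44.1 | (2/3)² = 44.4% | 53.3 |
| 2 | exp(−2) = 13.5% | 5.4 | 16.2 | (2/4)² = 25.0% | 30.0 |
| 3 | exp(−3) = 5.0% | 2.0 | 6.0 | (2/5)² = 16.0% | 19.2 |

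**4. Effect of emergency laxatives.** Suppose a fraction r of participants with an otherwise empty week pass an assisted stool and that stool is scored. The Poisson totals are then multiplied by (1 − r). At r = 0.8 they become 44.1 × 0.2 = 8.8, 16.2 × 0.2 = 3.2 and 6.0 × 0.2 = 1.2 of 120. At r = 1 they are 0. The article gives no information on r.

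**5. Precision if these participants are left out.** The pairwise standardized difference detectable with 80% power at two-sided 0.05 is (1.960 + 0.842) × √(2/n):

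- n = 40: 0.63
- n = 35 (roughly m = 2, no rescue): 0.67
- n = 30: 0.72
- n = 25 (roughly m = 1, no rescue): 0.79

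The per-protocol restriction may already bring n below 40.

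**6. What a period mean would keep.** At an unchanged rate, the probability of no stool in 4 weeks is exp(−4m): exp(−4) = 1.8% at m = 1 and exp(−8) = 0.03% at m = 2. A mean over weeks 1-4 is then available for nearly everyone.

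**The case against.** A reader might infer that the most constipated patients drop out of both outcomes. The article does not say so. No passage removes a participant for want of a baseline score, and the per-protocol definition does not ask for one. Emergency drugs are exempt from the pre-randomization restriction, and the bar on assisted movements is written only for the spontaneous counts. Read literally, an assisted stool can supply a score, so the relevant event is a week with no stool of any kind. This stands: the count affected starts at zero, and the Poisson figures without rescue are not an estimate for this trial.

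A reader might also infer bias between arms. That does not follow either. The baseline diary precedes allocation, so any loss from it is balanced in expectation. The primary outcome is a count and is unaffected.

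It can further be said that an undefined secondary baseline is a detail for an analysis plan that is not shown. This holds in part: the handling could be set out there. But the article itself fixes the change definition, the baseline window and the imputation rule, and a plan that kept all three would still have no value for such a participant.

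Nor does the laxative provision settle the matter. It permits use and does not ensure it, and its text sits under Intervention rather than baseline. If assisted stools are scored, some baseline values would describe a laxative or enema stool, which also needs to be known when the change is read.

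**Conclusion.** The point holds in a limited form. For a participant with no stool in the 1-week baseline diary, the change in mean Bristol score and the change in mean straining score are undefined, and the stated missing-data rule cannot repair this. Whether laxative-assisted stools are scored is not stated, and that choice largely determines how often the gap arises.

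The size cannot be derived from the article. It rests on an assumed stool rate and an unknown rescue fraction: about 37% to 5% for Poisson means of 1 to 3 per week without emergency laxatives, higher if rates vary between patients, and falling towards 0 if assisted stools are scored. The consequence is reduced precision and representativeness in two secondary outcomes, concentrated among the more severely constipated. It is not a threat to the between-arm comparison or to the primary outcome.

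**What to change.** In Secondary outcome measures and Statistical analysis:

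1. Define both outcomes as the mean score over weeks 1-4 and the mean score over weeks 5-8, in place of change from baseline.
2. Compare arms on these means with the baseline score as a covariate. Where no baseline score exists, set it to a constant and include a no-baseline-stool indicator. This is acceptable here because the gap arises before allocation.
3. State whether laxative-assisted stools are scored, and apply the same rule at baseline and in both periods.
4. Report by arm the number of participants without a scorable baseline.

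The cost is a reworded definition of two secondary outcomes and slightly more analysis work; no new data are needed. A participant with no scored stool throughout a 4-week period would still have no value, but on the assumed rates this is rare. Lengthening the baseline diary is not recommended: at a mean of 1 per week, two weeks would still leave exp(−2) = 13.5% empty, and randomization would be delayed by a week.

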#### Inclusion criteria

Inclusion criteria are a diagnosis of ischemic stroke according to the diagnostic criteria specified by the World Health Organization [23], constipation symptoms according to the Rome IV Functional Constipation Criteria [24], 2 weeks to 6 months after stroke onset, aged between 30 and 75 years old, Glasgow Coma Scale score ≥ 7 and National Institute of Health Stroke Scale ≤ 21, no previous medical history of constipation before stroke onset and symptoms of constipation present for at least 2 consecutive weeks after stroke, no use of gastrointestinal drugs 1 week before randomization (except for emergency drugs), no acupuncture treatment for constipation in the previous 2 weeks, and signed informed consent form.

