## Methods/design

### Study design

This is a prospective parallel-arm randomized controlled pilot trial comparing acupuncture with a pharmacological intervention (mosapride citrate) and usual care (control group). We will recruit patients who have sustained an ischemic stroke and present with constipation, according to predefined inclusion and exclusion criteria, between January 2017 and September 2019. Participants will be randomly allocated to one of three groups and will receive continuous treatment for 4 weeks. Repeat assessments will take place after treatment and later, at 8 weeks after inception. All participants will be asked to keep a defecation diary including weekly number of complete spontaneous bowel movements (CSBMs), SBMs, stool consistency, defecation difficulty, and laxative use and dosage, beginning at baseline during the 8-week assessment period. All outcomes will be assessed at baseline, and at 4- and 8-weeks after randomization, according to the defecation diary (Fig. 1).

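### Entry limits on consciousness and stroke severity do not ensure that a randomized patient can give the self-report on which the primary endpoint depends

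*Protocol article*

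**What the plan says.** All references are to the protocol article.

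- **Entry.** Inclusion criteria requires "Glasgow Coma Scale score ≥ 7 and National Institute of Health Stroke Scale ≤ 21". Recruitment and baseline assessment has a neurologist determine both scores and adds that "these scores will be used to decide whether to include the patient in the study".
- **Primary endpoint.** Primary outcome measure defines it as "the change in the weekly mean number of CSBMs over the 4 weeks of the intervention and the 4 weeks of the follow-up". A complete spontaneous bowel movement (CSBM) is a spontaneous movement "accompanied by a self-reported feeling of complete evacuation".
- **Data source.** Study design states: "All participants will be asked to keep a defecation diary including weekly number of complete spontaneous bowel movements (CSBMs), SBMs, stool consistency, defecation difficulty". The same section takes all outcomes at baseline, week 4 and week 8 from this diary. The patient completes it for one week at baseline (Recruitment and baseline assessment).
- **Indirect filters.** A signed consent form is an inclusion criterion, with no signatory specified. Randomization and allocation concealment has the envelope opened only once baseline measurements exist.
- **What the criteria do not address.** Neither the inclusion nor the exclusion criteria mention ability to communicate, aphasia or cognitive capacity. No section mentions a caregiver or other proxy answering the diary.

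**The concern.** The entry filter measures consciousness and neurological deficit, whereas the endpoint needs a sensation reported by the participant. These are different properties, and the article does not connect them. A patient can meet both score limits and still be unable to say whether evacuation felt complete.

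The stake is the purpose of the trial. Sample size and Discussion say that the study exists to supply effect sizes, variability and information on data completeness for later trials. A randomized participant who cannot report adds no information on the primary effect. Depending on how the blank is handled, that participant becomes missing data, a caregiver's guess at a sensation in a trial where participants are unblinded, or an apparent zero change. The first costs precision, the second adds error that may differ by arm, and the third dilutes the mean difference.

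**Working it through.** **Step 1. The plan's own figure.** 3 groups × 40 = 120, as stated. It was chosen for practical reasons; no effect size, SD or power is given, so there is no power calculation to reproduce.

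**Step 2. Do the limits admit patients who cannot report?** The structure of the Glasgow Coma Scale is general knowledge and is not in the article. The total is eye + verbal + motor, with eye ≥ 1 and verbal ≥ 1. At a total of 7, motor is at most 7 − 1 − 1 = 5, one short of the maximum of 6, which is obeying commands. The NIHSS limit is also a total score with language as one component, so marked aphasia can lie within it. Neither limit tests ability to report.

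**Step 3. Does another step close the gap?**

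| Step in the article | What it screens | What it leaves open |
|---|---|---|
| Signed consent form | Patients who cannot consent, if they must sign themselves | Signatory and capacity not stated |
| 1-week baseline diary | Patients with no diary at all | No rule on a diary lacking self-reported evacuation answers |
| Envelope opened after baseline measurements | Order of events | Not stated that an unusable diary stops allocation |

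A diary with no CSBMs also looks like a plausible baseline in a constipated patient, so the problem need not be noticed.

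**Step 4. What happens to such a patient once randomized?** The article does not say how an unanswered evacuation item is scored.

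- *Treated as missing:* Statistical analysis replaces missing data with the last measured value. If that is the baseline value, the change is zero. If there is no valid value, nothing can be carried forward.
- *Counted as not complete:* zero CSBMs throughout, hence zero change.
- *Answered by a caregiver:* not a self-report under the stated definition.

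**Step 5. Size if they count as zero change.** Let q be the share unable to report, assumed equal across arms. The remainder have mean change μ and SD σ.

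- Observed arm mean: (1 − q)μ, so a difference between arms shrinks by the fraction q.
- Observed variance: (1 − q)(σ² + μ²) − (1 − q)²μ² = (1 − q)σ² + q(1 − q)μ².
- Required sample size is proportional to variance / difference². Relative to patients who can report, the factor is (1 + q·μ²/σ²)/(1 − q), with μ²/σ² averaged over the two arms compared.

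| q (assumed) | μ = 0 | μ = 0.5σ |
|---|---|---|
| 10% | 1/0.9 = 1.11 | (1 + 0.1 × 0.25)/0.9 = 1.14 |
| 20% | 1/0.8 = 1.25 | (1 + 0.2 × 0.25)/0.8 = 1.31 |

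**Step 6. Size if they are excluded as unmeasurable.** The 95% half-width for a pairwise difference is 1.96 × √(2/n) in SD units.

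| q (assumed) | n per group | Half-width (SD) | Recruits per group to keep 40 measurable |
|---|---|---|---|
| 0% | 40 | 0.44 | 40 |
| 10% | 36 | 0.46 | 40/0.9, rounded up: 45 |
| 20% | 32 | 0.49 | 40/0.8 = 50 |

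**The case against.** The strongest reply is that few such patients would ever be randomized. Patients sign consent, fill in an information form and keep a diary for a week before any envelope is opened. They are 2 weeks to 6 months after stroke and come from acupuncture clinics and wards, partly through posters and a website, and follow-up involves a telephone interviewer. A patient who cannot follow commands is unlikely to complete that path. This largely stands: it makes a small q plausible, and baseline is where most of these patients would drop out. It does not close the gap, because none of these steps is stated as a condition on ability to report.

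A second reply is that the article condenses a fuller protocol, which may say who signs and what makes a diary unusable. That is possible. But the entry limits and the endpoint definition are both stated here, and as stated they do not fit together.

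A reader might also infer more than the text supports:

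- *That these patients necessarily score zero at every visit.* The article has no such scoring rule. It is one of three possibilities.
- *That the straining score fails in the same way.* Secondary outcome measures says only that "The severity of straining will be graded using a 5-point ordinal scale" and names no rater. Self-report there is inferred from defecation difficulty being a diary item. For the CSBM it is explicit.
- *That a later trial would be inflated by 1/(1 − q)², or 1.23 and 1.56 at 10% and 20%.* That holds the SD fixed, although zero-change patients alter it. The two formulas agree only when μ²/σ² = 1/(1 − q), a mean change slightly above 1 SD.
- *That any later trial would be oversized.* If it kept the same entry criteria, the diluted effect would be the right one to plan on.

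**Conclusion.** The mismatch is real but limited. The article filters entry on two scores that do not establish ability to report, defines its primary endpoint by self-report, and makes no usable self-reported diary a condition of allocation. Its size cannot be determined from the document, because q is not given and may be small.

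Under the zero-change assumption, with q of 10% or 20% and a mean change of 0 to 0.5 SD, a later trial in patients who can report would be too large by a factor of about 1.11–1.14 or 1.25–1.31. Under exclusion, the pairwise half-width rises from 0.44 to 0.46 or 0.49 SD. These ranges illustrate the consequence and do not predict it.

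It should be fixed because the remedy is cheap and a missing self-report cannot be recovered after randomization. Calling it critical is not supported: existing steps probably remove many of these patients, and nothing in the document indicates that the remaining share is large.

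**What to change.** Reconcile Inclusion criteria with Study design and Primary outcome measure by adding one inclusion criterion: the patient can answer the diary's self-report items, either in their own writing or by their own verbal or yes/no answer transcribed by a caregiver. Confirm this on the 1-week baseline diary before the envelope is opened, and state that a diary without the patient's own evacuation answers does not permit allocation. The Glasgow Coma Scale and NIHSS limits can stay as they are.

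The check uses data already collected, so it needs no new visit or instrument. The cost is a slightly narrower population and the loss of a few recruits, who could not have contributed valid primary data.
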